# Effect of electroacupuncture versus prucalopride for severe chronic constipation: protocol of a multi-centre, non-inferiority, randomised controlled trial

**DOI:** 10.1186/1472-6882-14-260

**Published:** 2014-07-23

**Keywords:** Acupuncture, Prucalopride, Severe chronic constipation

## Abstract

**Background:**

Acupuncture is safe and may be effective for severe chronic constipation. The World Gastroenterology Organisation recommends prucalopride for patients for whom previous laxative use failed to provide satisfactory relief.

**Methods/design:**

In this prospective, multi-centre, randomised controlled trial, five hundred sixty patients with severe chronic constipation (two or less spontaneous complete bowel movements per week) from 14 centres will be randomised to receive either electroacupuncture or prucalopride. Participants in the electroacupuncture group will receive electroacupuncture for eight weeks, while participants in the control group will take prucalopride (2 mg once daily) for 32 weeks. The primary outcome measure is the proportion of patients having ≥3 spontaneous, complete bowel movements per week, averaged over week three to eight. The secondary outcome measures include eight items, including the proportion of patients having ≥3 spontaneous, complete bowel movements per week averaged over week 9–32, the proportion of patients with one or more increases in spontaneous, complete bowel movements per week from baseline, mean Bristol Stool Scale, etc. Statistical analysis will include the CMH test, nonparametric tests and t tests.

**Discussion:**

We aimed to compare the effect of electroacupuncture versus prucalopride for severe chronic constipation. The limitation of this study is that participants and acupuncturists will not be blinded.

**Trial registration:**

ClinicalTrials.gov Identifier: NCT02047045.

## Background

Twelve percent of adults have constipation worldwide [1]. In China, the figure is 4%-6% [2, 3]. Severe chronic constipation is defined as two or fewer spontaneous, complete bowel movements (SCBMs) per week, hard stool and a sensation of straining during defecation [4]. Due to their widespread use, laxatives are an available choice for constipated patients. However, a high level of dissatisfaction has been reported for laxatives; specifically, evidence supporting the lasting effect of laxatives is limited [5–7]. A study of PEG3350 showed that 38.4 ± 14.1 days after the cessation of PG3350, 29 of 47 (61.7%) patients needed to take additional constipation treatment interventions [8]. A survey of 744 patients with chronic constipation in Europe showed that almost half were using alternative treatments (homeopathy, massage and acupuncture), and nearly 90% of respondents expressed interests in new therapies [6].

With a history of thousands of years, acupuncture has long been used to treat constipation in China. The systematic review [9] we have published concluded that acupuncture was safe for chronic functional constipation and might improve weekly spontaneous bowel movements (SBMs), the quality of life, and relevant symptoms. However, the evidence was limited by the small sample size and the methodological quality. A pilot study (n = 60) we have finished showed that 31.67% patients had 3 or more weekly SBMs after 8 weeks of treatment. By the third month, 40% patients still had 3 or more weekly SBMs, which reflected the lasting effect (effect post treatment) of acupuncture (to be published).

This report is a protocol of a phase-II trial aiming to evaluate the effect of electroacupuncture (EA) versus prucalopride for severe chronic constipation. The World Gastroenterology Organisation recommends prucalopride for patients for whom previous laxative use failed to provide satisfactory relief [10]. It was also considered effective and safe in a randomised controlled trial conducted in the Asia-Pacific region [11]. Thus, the use of prucalopride as the control drug in this trial is reasonable. The objective is to compare the effect of EA versus prucalopride for severe chronic constipation. We will also observe how many patients will not need additional medicine until the 3^rd^ and 6^th^ month post treatment. The safety and acceptance of EA will be simultaneously evaluated.

## Methods/design

### Study design

This study is a prospective randomised controlled trial. It will be conducted from April 2014 to August 2015 at 14 hospitals around China^a^. Five hundred and sixty participants are planned to be recruited via advertisements in newspapers, television, websites and posters. After being diagnosed by physicians of the gastroenterology or anorectal departments, participants will receive a 2-week long assessment (the stool diary). Randomisation will be performed centrally by the Clinical Evaluation Centre of the China Academy of Chinese Medical Sciences in Beijing, and eligible participants will be randomised into the EA group or the control group. After the baseline assessment has been carried out and the informed consent has been obtained, a randomisation number will be sent to the acupuncturist by phone or online. The statisticians, outcome assessors, and physicians will be blinded to the allocation. The flowchart of the trial is presented in Figure 1. The duration of the trial is 34 weeks, including a 2-week long baseline assessment period (week-2-0), 8-week long treatment period (week 1–8), and 24-week long follow-up period (week 9–32). The time frame of the trial is presented in Figure 2. The trial protocol is in accordance with the principles of the Declaration of Helsinki and has been approved by the review board and ethics committee of the participating hospitals.

**Figure 1 Fig1:**
[figure not shown]
**The flowchart.**

**Figure 2 Fig2:**

**Time Frame of the Trial.**

### Participants

Five hundred and sixty participants met the Rome III criteria [12] are planned to be recruited.

Inclusion criteria: 1) Primary chronic constipation meeting the Rome III criteria, with ≤2 SCBMs (SCBM refers to the feeling of complete evacuation after a bowel movement without the help of drug or hands in the past 24 hours. Bowel movement beyond 24 hours after the use of medicine/hands also could be considered a SCBM). They should conform to at least one of the following items at the same time: a. a feeling of straining during evacuation (at least once per 4 bowel movements); b. lumpy or hard stools (at least once per 4 bowel movements); c. a feeling of incomplete evacuation after a bowel movement (at least once per 4 bowel movements); d. a feeling of obstruction in the anus/rectum (at least once per 4 bowel movements); e. needing the help of hands for evacuation (at least once per 4 bowel movements). 2) Participants who do not meet the diagnosis of irritable bowel syndrome (IBS). 3) Previous laxative use failed to provide satisfactory relief. 4) Patients aged 18 to 75 years old. 5) Two or fewer SBMs per week during the 2-week long baseline assessment. 6) No use of medicine for constipation during the 2 weeks before enrolment (except rescue medication usage); no acupuncture treatment for constipation in the previous 1 month; no participation in any other on-going trial. 7) Volunteered to join this trial and signed the informed consent.

Exclusion criteria: 1) Irritable bowel syndrome, organic constipation or secondary constipation caused by endocrine, metabolic, nervous, postoperative diseases, or drugs; 2) More than one mushy or watery stool during baseline while not taking laxatives (Bristol stool type 6 or 7); 3) A history of pelvic floor dysfunction; 4) Taking medicine that can influence the intestinal function or induce constipation; 5) Severe haemorrhoid or anal fissure; 6) Patients with severe cardiovascular, hepatic or renal diseases, cognitive impairment, abdominal aortic aneurysm or hepatosplenomegaly, aphasia, mental disorders, or illness that will influence the examination or treatment; 7) Women in the gestation or lactation period; 8) Patients with blood coagulation disorders or taking anticoagulants regularly, such as Warfarin and Heparin; 9) Patients with a cardiac pacemaker carrier.

### Intervention

All participants will be advised of lifestyle modification, such as maintaining their original lifestyle, avoiding fibre-rich food or following a weight-loss diet. Therapies other than the treatment regimen are prohibited during the trial.

#### Treatment group

The acupuncture regimen is based on the Chinese literature from the past 20 years, our pilot trial and specialist consensus. The point regimen (points used for every participants of EA group) includes bilateral ST25, SP14 and ST 37. Moreover, BL33, DU20 and DU24 could be used according to the individual situation. BL 33 could be used for straining and incomplete evacuation. DU20 and DU24 could be used for anxiety and depression.

For ST25 and SP14, the needle will be inserted vertically to the abdominal muscles. The acupuncturist can feel resistance from the tip of the needle when touching the muscles and continues to insert it to a depth of 2–3 mm and stops. For ST 37, the needle will be inserted vertically to a depth of 25 mm. The needle will be manipulated with an even lifting and twisting method three times to achieve the sensation of deqi (patients having a sour and distension sensation). For DU20 and DU24, the needle is obliquely inserted back towards the galea aponeurotica to a depth of 40 mm. The needle is manipulated with an even lifting and twisting method three times to achieve the sensation of deqi. If BL33 is needed, all points could be simultaneously needled when participants are in the lateral decubitus position. The site 0.5-1 cm outside and above the 3rd posterior sacral foramina will serve as the inserting site. The needle is inserted at the inserting site inward and downward at a 30–45 degree angle to a depth of 50–60 mm.

An electric stimulator will be placed on the pair of ST25 and SP14 points with a spare-dense wave, 10/50 Hz, 0.1–1.0 mA (for BL33, the intensity is 0.5-2.0 mA). For ST37, DU20 and DU24, the needles will be manipulated with an even lifting and twisting method every ten minutes, and three manipulations will be used for each participant in all. Patients will be given one session per day for 30 min, 5 sessions/week for the first 2 weeks, and 3 times/week for the next 6 weeks.

#### Control group

Prucalopride Succinate (Janssen S.P.A) will be taken orally at a dose of 2 mg/day before breakfast for 8 weeks. Participants will undergo an electrocardiogram (ECG) at the 8^th^ week, and the drug will be taken for another 24 weeks in the absence of adverse events (like Q-T elongation).

The use of other medicine for constipation will not be allowed during the trial. Bisacodyl (5–10 mg) and Enemia Glycerini (110 ml) can be used for participants who fail to have a bowel movement for 3 or more consecutive days. Furthermore, the use of Bisacodyl and Enemia Glycerini should be recorded on the case report form.

### Outcome measures

The outcome measures are based on the stool diary. The participants complete a stool diary, which is checked by outcome assessors and finally recorded in the Remote Data Capture (RDC) system. The contents of the stool diary include SBMs within 24 hours, straining degree, complete evacuation, stool consistency, use of drugs, etc. Participants will be asked to finish the diaries every day during the baseline assessment period, week 1–8, 11–12, 15–16, 19–20 and 31–32.

This trial includes one primary outcome measure and 8 secondary outcome measures. The primary outcome is the proportion of patients having ≥3 SCBMs/week, averaged over week 3–8. The secondary outcome measures are presented in Table 1. The safety of EA will be evaluated based on various events, including fainting, severe pain, haematoma, local infection, and any feeling of discomfort. The side effects of prucalopride include diarrhoea, nausea, abdominal pain, headache, palpitation, myocardial ischemia (presented in ECG), etc. Any adverse event resulting from EA or adverse drug reaction will be recorded.

**Table 1 Tab1:** **Secondary outcome measures**

No.	Outcome measure	Time frame	Statistics
1	Proportion of patients having ≥3 SCBMs/week	Week 1–2, week 9–12, week 9–16, week 9–20, week 9-32	CMH test
2	Proportion of patients with one or more increase in SCBMs/week from baseline	Week 1–2, week 3–8, week 9–12, week 9–16, week 9–20, week 9-32	CMH test
3	SCBMs/week and change from baseline	Week 1–2, week 3–8, week 9–12, week 9–16, week 9–20, week 9-32	Nonparametric test
4	SBMs/week and change from baseline in SCBM/week	Week 1–2, week 3–8, week 9–12, week 9–16, week9-20, week 9-32	Nonparametric test
5	Mean Bristol Stool Scale and change from baseline	Baseline, week 1–2, week 3-8	Nonparametric test
6	Straining degree	Week 1–2, week 3–8, week 9–12, week 9–16, week 9–20, week 9-32	Nonparametric test
7	Time to first SCBM	Time from the first treatment to the first SCBM	Nonparametric test
8	Patient assessment of Constipation Quality Of Life (PAC-QOL)	Baseline, week 1–4, week 5-8	*t* test or Mann–Whitney *U* test

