## Discussion

Acupuncture has been used to treat constipation in China for thousands of years. Clinical practice and several trials showed that acupuncture is effective for constipation [13, 14]. However, the effect of acupuncture on severe constipation has not been evaluated. A protocol of EA versus sham acupuncture for severe constipation has been published [15].

This is a study design for a non-inferiority, randomised controlled trial aimed to compare the short-term effect (the 3^rd^ to 8^th^ treatment week) of EA with prucalopride for severe chronic constipation. Acupuncture is a non-toxic, economical intervention with minimal adverse effects [16]. If the efficacy of EA is non-inferior to prucalopride, it may be a reasonable option for patients who do not want to experience the side effects of prucalopride. We also want to observe EA’s lasting effect, i.e., EA’s effect at the 3^rd^ and 6^th^ month post treatment. The EA group will be treated for 8 weeks and the prucalopride group will be treated for 32 weeks. A comparison between the two groups after the 8^th^ week could clarify the lasting and dominant effect of EA.

This trial was limited because the participants and acupuncturists could not be blinded. However, the outcome assessors and statistician will be blinded to the allocation.

In conclusion, the trial will compare the effect of EA to that of prucalopride for severe chronic constipation.

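### Table 1 has no outcome that isolates the 3rd- or 6th-month effect the protocol wants to observe, because every follow-up window starts at week 9 and averages in earlier diary weeks

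*Protocol article*

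**What the plan says.** The Study design section sets a "24-week long follow-up period (week 9–32"). The Outcome measures section states that "The outcome measures are based on the stool diary", and fixes the diary calendar: "Participants will be asked to finish the diaries every day during the baseline assessment period, week 1–8, 11–12, 15–16, 19–20 and 31–32".

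Table 1 gives the windows for the first secondary outcome (proportion with at least 3 SCBMs/week) as "Week 1–2, week 9–12, week 9–16, week 9–20, week 9-32". Items 2, 3, 4 and 6 have the same four follow-up windows. Items 5 and 8 end at week 8, and item 7 is time to first SCBM. The abstract names the long window first among the secondary outcomes and makes clear that it is an average: "the proportion of patients having ≥3 spontaneous, complete bowel movements per week averaged over week 9–32".

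The aims are put in terms of time points. The Discussion describes the lasting effect of interest as electroacupuncture's "effect at the 3^rd^ and 6^th^ month post treatment", and expects the comparison after week 8 to clarify it. The Background adds a related aim, "We will also observe how many patients will not need additional medicine until the" 3rd and 6th month after treatment. Electroacupuncture is given for 8 weeks and prucalopride for 32.

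**The concern.** The aim concerns the state of patients at two times: about week 20 (8 + 12) and week 32 (8 + 24). The outcomes are running averages from week 9. Each later window contains all the earlier ones, so the longest window is not a month-6 measurement, although its place in the abstract invites that reading.

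The two arms are also treated differently in this period. Electroacupuncture has stopped and prucalopride continues, so waning after the end of treatment is to be looked for mainly in the electroacupuncture arm. If it occurs late, the average mixes it with better earlier weeks and makes the effect look more durable than it is at month 6. The credibility of a lasting-effect statement is at stake, not the non-inferiority conclusion.

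**Working it through.** **Inputs.** Follow-up is weeks 9–32 (Study design). Follow-up diaries are kept in weeks 11, 12, 15, 16, 19, 20, 31 and 32 (Outcome measures). The response threshold is 3 SCBMs/week (Table 1, item 1), applied to an average (abstract).

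**The plan's own figure.** 32 − 9 + 1 = 24 weeks, as the article states.

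**Coverage.** Diary weeks are 4 × 2 = 8, and 8/24 = 33%. Weeks 9–20 hold 6 of the 8 (75%) and weeks 21–32 hold 2 (25%). Weeks 21–30 have none.

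**Weight of the latest block**, if each observed week counts equally (an assumption): 2 ÷ diary weeks in the window.

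| Window | Diary weeks / calendar weeks | Latest block | Its weight |
|---|---|---|---|
| 9–12 | 2 / 4 | 11–12 | 2/2 = 100% |
| 9–16 | 4 / 8 | 15–16 | 2/4 = 50% |
| 9–20 | 6 / 12 | 19–20 (month 3) | 2/6 = 33% |
| 9–32 | 8 / 24 | 31–32 (month 6) | 2/8 = 25% |

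So week 9–12 is in fact weeks 11–12, and the two time points named in the aim carry a third and a quarter of the windows that end on them.

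**One patient.** With 4 SCBMs/week in the first three blocks and none in weeks 31–32, the average is (4 × 6 + 0 × 2)/8 = 3.0. This patient is a week 9–32 responder with no SCBM at month 6. With 4 and then 1, the average is (24 + 2)/8 = 3.25, with the same result.

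**Groups (illustration; the rates are assumptions, not trial data).** Each patient's weekly rate is the block mean times a gamma variable with shape 1.5 and mean 1. Counts are Poisson and observed weeks are weighted equally.

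| Mean SCBMs/week in the four blocks | Responders, week 9–32 | Responders, weeks 31–32 |
|---|---|---|
| 2.5, 2.3, 2.1, 1.0 (sharp late fall) | 22% | 7% |
| 2.5, 2.3, 2.1, 1.9 (mild decline) | 26.5% | 24.6% |
| 2.3 throughout (flat) | 28% | 32% |

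The first row shows a large overstatement and the second a small one. In the third the sign reverses, because a two-week count is noisier and the threshold lies above the mean, so more patients cross it by chance.

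**Precision.** With independent weeks of equal variance, the within-patient sampling variance of a 2-week mean is 8/2 = 4 times that of an 8-week mean.

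**The case against.** A reader might infer that relapse by month 6 is hidden and the lasting-effect question cannot be answered. The documents do not support that. Table 1 reports both week 9–20 and week 9–32, so a late fall shows as a drop between them; in the sharp-fall scenario responders go from about 29% to 22%. For the means, with complete data and equal weights, the late block can even be recovered: mean(31–32) = 4 × mean(9–32) − 3 × mean(9–20). This stands, and the right word is diluted. The recovery does not work for responder proportions, however, and gives no confidence interval for the difference between arms.

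A reader might also infer that the windows overstate electroacupuncture's durability as a matter of fact. That needs late waning, which the documents do not show. The pilot figures in the Background rise, from 31.67% after 8 weeks to 40% by the third month, though for SBMs rather than SCBMs and with nothing on month 6. The direction is therefore conditional.

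Three further points have force. The article does not say how diary blocks are combined. Weighting by calendar time would give weeks 31–32 half the weight of week 9–32, and the patient at exactly 3.0 would drop out. Intermittent diaries are an ordinary way to limit burden, and the first three windows are each sampled at an even 50%. Finally, the Discussion presents the trial as a short-term comparison, with the lasting effect as something additionally to be observed. These points limit the size and rank of the issue. They do not supply a month-3 or month-6 outcome.

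**Conclusion.** The point holds as a mismatch between a stated secondary aim and the outcomes listed for it. The counts are exact: 8 of 24 follow-up weeks have diaries, 6 of the 8 fall in the first half, and no Table 1 outcome isolates month 3 or month 6. The weights of 33% and 25% rest on equal weighting of observed weeks. Any flattering of the electroacupuncture arm rests on late waning. Under the illustrative model the gap between the week 9–32 and weeks 31–32 responder rates runs from 15 percentage points (22 − 7) to −4 (28 − 32).

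The windows are fixed in the article's own table, so this is not a detail left to an analysis plan. The primary outcome, over weeks 3–8 with a diary in every week, is unaffected. The change is worth making, but the trial's main conclusion does not depend on it.

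**What to change.** 1. Keep the cumulative windows, including the week 9–32 outcome named in the abstract. For items 1–4 and 6 add weeks 19–20 and weeks 31–32 as prespecified stand-alone outcomes for months 3 and 6, each with the difference between arms and a 95% confidence interval.
2. Base any statement about a lasting effect on these two blocks. Compare the arms within a block; do not set a 2-week responder rate against an 8-week one, since they differ by noise alone.
3. State that week 9–12 and the other follow-up windows are computed from the observed diary weeks only, and how those weeks are weighted.
4. Optionally, to serve the Background's aim on additional medicine, report the proportion with no recorded use of bisacodyl or glycerin enema up to weeks 20 and 32. Study prucalopride must not count, because controls may take it to week 32. The case report form is the source; diary entries on drug use cover only the 8 diary weeks.

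Cost: no new diary data are needed. The change amends the secondary outcomes of a registered trial, best made early; the article reports nineteen participants recruited. It adds 5 items × 2 time points = 10 outcome-by-time entries, and each block has about four times the within-patient sampling variance of the 8-week average, so intervals will be wider.

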### Data collection and quality control

Two researchers will independently input the data using the Remote Data Capture (RDC) software. A Data Verification Plan (DVP) will be established to review the data after input. Two data managers with a medical background will code the medical history, adverse events and drug combinations. After a data review, the data will be submitted to the statistician for final analysis.

A rigorous methodology will be followed to guarantee the quality of the trial. Before commencing the trial, experts in different fields will be invited to review and revise the protocol, and staff from the 14 trial centres will undergo training. A 3-level monitoring system will be established to periodically assess the performance of the trial. The outcome assessments, the completion of case report forms and data management will be closely supervised.

### Sample size and statistical analysis

The sample size will be based on the primary outcome (the proportion of patients having ≥3 SCBMs/week averaged over week 3–8). According to our pilot trial and the literature [4], the proportion of participant having ≥3 SCBMs averaged over week 3–8 was 31.6% for the EA group and 30.9% for the prucalopride group. The figure for the placebo group was 12.0% [4]. Thus, a non-inferiority margin of 10% is reasonable. To assess the non-inferiority between the treatment and control groups, a sample size of 276 for each group will be sufficient, with a one-sided 5% level of significance, a power of 80% and allowing for a 20% dropout. In this trial, we aim to recruit 560 participants, 40 for each hospital.

The data from the 14 centres will be pooled, and the Clinical Evaluation Centre of the China Academy of Chinese Medical Sciences in Beijing will conduct the statistical analysis using the SAS 9.1.3 (SAS Institute, Cary, NC, US) and SPSS Ver.13.0 (SPSS Inc., Chicago, IL, USA) software. The data analysis is based on the intention-to-treat (ITT) population. All statistical analyses will be two-sided tests except for the primary outcome. The level of significance will be established at 0.05. Continuous data will be represented by the mean, standard deviation, median, minimum value, and maximum value; categorical data will be represented by percentages. To compare two independent samples, a t-test or nonparametric test will be used for continuous data, and a chi-square test/the Fisher exact test/nonparametric tests will be used for categorical data. For the primary outcome, the CMH test will be used to avoid the centre effect. The analysis methods for secondary outcomes are presented in Table 1. For safety analysis, the incidence of adverse events will be compared between the two groups using the chi-square test or the Fisher exact test.

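### One pilot figure appears under two outcomes and two time windows, so the stated 80% power is unsupported until the two sections are reconciled

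*Protocol article*

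**What the plan says.** The Background of the protocol article describes the sponsor's own pilot: "A pilot study (n = 60) we have finished showed that 31.67% patients had 3 or more weekly SBMs after 8 weeks of treatment". The outcome there is spontaneous bowel movements (SBMs), measured after eight weeks.

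The section on sample size and statistical analysis names the pilot and one literature source as the basis for its rates. It states that "the proportion of participant having ≥3 SCBMs averaged over week 3–8 was 31.6% for the EA group and 30.9% for the prucalopride group", gives 12.0% for placebo, and judges that "a non-inferiority margin of 10% is reasonable". It concludes that "a sample size of 276 for each group will be sufficient". The settings behind that size are a one-sided test at 5%, 80% power and an allowance of 20% for dropout. Recruitment is set at 560.

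The primary outcome, under Outcome measures, is three or more spontaneous, complete bowel movements (SCBMs) per week, averaged over weeks 3–8. The article treats the two measures as distinct: inclusion criterion 1 ties an SCBM to a feeling of complete evacuation, the abbreviation list defines the terms separately, and Table 1 gives them separate rows. No other pilot rate for SCBM response over weeks 3–8 appears anywhere.

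**The concern.** The two sections share a source and, apart from the last digit, a number. They differ on what was counted and when. Both descriptions cannot be right for the same figure.

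The plan needs EA to be slightly better than prucalopride (31.6% − 30.9% = 0.7 points). Non-inferiority power is very sensitive to that difference. An SCBM is an SBM that is also complete, so in the same patients over the same weeks the SCBM responder rate cannot exceed the SBM rate. If the Background label is correct, the EA input is probably too high for the endpoint being tested, while the prucalopride and placebo rates are presented as SCBM rates. A trial that then failed to show non-inferiority might simply have been too small.

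**Working it through.** **Inputs from the article.** Prucalopride rate pC = 0.309; EA rate pE = 0.316 (sample-size section) or 0.3167 (Background); margin 0.10; one-sided 5% (z = 1.645); power 80% (z = 0.842); dropout 20%; total 560. I assume 1:1 allocation, so 280 per arm, or 280 × 0.8 = 224 after dropout.

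**Formula (unpooled variance).** n per arm = (1.645 + 0.842)² × [pC(1 − pC) + pE(1 − pE)] / (0.10 + pE − pC)². The squared sum of z values, before rounding, is 6.183.

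**Step 1: reproduce the stated size.**
- With pE = 0.3167: 6.183 × (0.2135 + 0.2164) / 0.1077² = 229.2, rounded up to 230. Then 230 × 1.2 = 276, the stated size exactly.
- With pE = 0.316: 6.183 × (0.2135 + 0.2161) / 0.107² = 232.0, rounded up to 233. Then 233 × 1.2 = 279.6, or 280.

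The unrounded Background figure therefore gives the printed size, and the rounded figure gives a size within 2%. The arithmetic is not at fault. The question is what the input measures.

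**Step 2: remove the assumed EA advantage.** With both rates at 0.309: 6.183 × 0.4270 / 0.10² = 264.02, so 265 evaluable per arm.

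**Step 3: power over a range of EA rates.** Power = Φ{(0.10 + pE − pC) / √([pC(1 − pC) + pE(1 − pE)] / n) − 1.645}. For example, at equal rates with n = 224 the standard error is √(0.4270 / 224) = 0.0437, and Φ(2.290 − 1.645) = Φ(0.645) = 74%.

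| EA rate | Power, 224 per arm | Power, 280 per arm | Evaluable n per arm for 80% |
|---|---|---|---|
| 31.6% (as stated) | 79% | 86% | 233 |
| 30.9% (equal rates) | 74% | 82% | 265 |
| 29% (assumed) | 59% | 67% | 396 |
| 27% (assumed) | 41% | 48% | 683 |
| 25% (assumed) | 25% | 29% | 1475 |

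**Step 4: precision of the pilot.** 31.67% of 60 is 19 patients. The Wilson 95% interval for 19/60 is 21.3% to 44.2%.

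**The case against.** A reader might infer that the sample-size section took an SBM rate and relabelled it, and that the exact match at 276 proves this. It does not. The match shows which number was used, not which outcome it measured; an SCBM rate of 31.67% gives the same 276. The Background may instead have written SBM where SCBM was meant. The article mixes the terms elsewhere: inclusion criterion 1 counts SCBMs while criterion 5 counts SBMs, and row 4 of Table 1 pairs SBMs per week with a change in SCBMs. If the Background is the slip, the outcome label in the sample size is sound and only the time window remains to be reconciled.

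A reader might also treat 31.67% as a ceiling for EA. The bound is strict only within the same patients and weeks. The windows differ, and a 60-patient estimate has wide error, so it does not cap the true EA rate.

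Nor is 74% the one correct power. The article bases its analysis on the intention-to-treat population. If all 280 per arm contribute, power at equal rates is 82%, above the stated target. Which figure applies depends on how dropouts are handled.

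These objections stand, and they limit the direction and size of the error. They do not remove the conflict between the two sections.

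**Conclusion.** The two sections contradict each other on an input that the sample size depends on. The stated 80% power is unsupported until they are reconciled. This is an inconsistency of labelling, not of arithmetic.

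If the Background is right, the EA rate is probably too high and unlike quantities are compared. If the sample-size section is right, the outcome is sound and the Background needs correcting. The documents do not settle which.

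The effect on power could be small or large. Losing only the 0.7-point advantage costs about five points of power with 224 per arm (79% to 74%) and about four with 280 (86% to 82%). Larger losses arise only at EA rates that are assumed for illustration; the article gives no evidence that EA responds at 29% or below. All figures assume 1:1 allocation, prucalopride at 30.9% and the unpooled formula.

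**What to change.** Re-tabulate the existing pilot records for three or more SCBMs per week averaged over weeks 3–8, and correct whichever section is mislabelled, including its time window.

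- If the figure proves to be an SBM rate, recompute the sample size with the true SCBM rate and restate the power.
- If the pilot did not record completeness, drop the assumed EA advantage and restate the power at equal rates of 30.9% with a sensitivity range such as the table above. Say whether it refers to 224 or 280 patients per arm.

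The cost is a review of 60 existing records and revised text. The article reports only nineteen participants recruited, so the correction comes early. The downside is that the stated power may look less favourable. Restating it needs no added patients. Holding 80% at equal rates after a 20% loss would need 265 evaluable per arm against the 224 expected, which is a separate decision for the sponsor.

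### The stated 276 per group does not cover a 20% dropout: on the printed inputs 292 are needed, and the planned 280 gives about 79% power (minor)

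*Protocol article*

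**What the plan says.** Everything needed stands in the protocol article, section Sample size and statistical analysis, apart from one figure in the Background.

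- **Response rates for the primary outcome:** "was 31.6% for the EA group and 30.9% for the prucalopride group".
- **Margin:** "Thus, a non-inferiority margin of 10% is reasonable".
- **Conclusion:** "a sample size of 276 for each group will be sufficient".
- **Error levels and loss on which that number is said to rest:** "with a one-sided 5% level of significance, a power of 80% and allowing for a 20% dropout".
- **Recruitment:** "we aim to recruit 560 participants, 40 for each hospital". With 14 hospitals and two equal groups this is 280 per group.
- **Likely source of the 31.6%**, in the Background: "A pilot study (n = 60) we have finished showed that 31.67% patients had 3 or more weekly SBMs after 8 weeks of treatment".

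The section names intention-to-treat as the analysis population. It gives no formula, no number before the dropout allowance, and no account of how the allowance was applied.

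**The concern.** If a fraction d of patients is lost, the number to randomise is the number needed for analysis divided by (1 − d). Multiplying by (1 + d) gives too few, because the loss applies to the enlarged number. At d = 0.20 the two factors are 1.25 and 1.20.

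Taking 20% off 276 leaves 220.8, and taking 20% off 280 leaves 224. If the formula needs more than 224, the statement that the size is sufficient for 80% power at 20% dropout is untrue both for the calculated number and for the recruitment target. This is the article's only justification of the trial's size, so the figure should hold on its own inputs.

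**Working it through.** **Inputs.** From Sample size and statistical analysis: EA rate 0.316, prucalopride rate 0.309, margin 0.10, one-sided 5% (z = 1.645), power 80% (z = 0.842), dropout 20%. From the Background: EA pilot rate 0.3167.

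**Formula** (difference of proportions, unpooled variance), evaluable patients per group:

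n = (1.645 + 0.842)² × [p₁(1 − p₁) + p₂(1 − p₂)] / (p₁ − p₂ + 0.10)²

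With unrounded z-values the first factor is 6.1826.

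**Reproducing 276.** With p₁ = 0.3167 and p₂ = 0.309:

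- variance sum: 0.21640 + 0.21352 = 0.42992
- distance to the margin: 0.0077 + 0.10 = 0.1077, squared 0.011599
- n = 6.1826 × 0.42992 / 0.011599 = 229.2, rounded up to 230
- 230 × 1.2 = 276, the stated number exactly
- 230 / 0.8 = 287.5, rounded up to 288

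**The rates as printed.** With p₁ = 0.316:

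- variance sum: 0.21614 + 0.21352 = 0.42966
- distance to the margin: 0.107, squared 0.011449
- n = 6.1826 × 0.42966 / 0.011449 = 232.02, rounded up to 233
- 233 × 1.2 = 279.6, rounded up to 280
- 233 / 0.8 = 291.25, rounded up to 292

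**Other formulas, printed rates, before the allowance:** pooled variance 232.0, Farrington–Manning 231.5, Dunnett–Gent 230.2. Multiplied by 1.2 they give 276–278; divided by 0.8 they give 288–290.

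**Power after 20% dropout**, from Φ[(p₁ − p₂ + 0.10) / √(variance sum / n) − 1.645]. Example for 224 at the printed rates: 0.107 / √(0.42966/224) = 2.443; 2.443 − 1.645 = 0.798; Φ = 78.8%.

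| Randomised per group | Left after 20% dropout | Power, EA 31.6% | Power, EA 31.67% |
|---|---|---|---|
| 276 | about 221 | 78.3% | 78.7% |
| 280 | 224 | 78.8% | 79.2% |

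**Dropout at which 80% power is still kept:**

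- 276 per group: 1 − 233/276 = 15.6%, or 1 − 230/276 = 16.7% with 31.67%
- 280 per group: 1 − 233/280 = 16.8%, or 1 − 230/280 = 17.9% with 31.67%

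**Gap to the planned 560:** 2 × 292 = 584, a gap of 24; or 2 × 288 = 576, a gap of 16.

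**The case against.** **The ×1.2 step is not in the document.** This stands. The exact match needs 31.67% in place of the printed 31.6%, and other routes cannot be excluded. For example, rates rounded to whole percents (32% and 31%) give 220.5, and 220.5 / 0.8 = 275.6, which also rounds up to 276. So the mechanism can only be called apparent. The shortfall does not depend on it: at the rates the article prints, 220.8 and 224 are both below 233, and below 230 too.

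**The analysis is by intention to treat, so dropouts may not be lost.** This stands in part. If every randomised patient were analysed at the printed rates, power would be about 86% at 276 or 280 per group. If, as an assumption, the 20% in each group were counted as non-responders (rates 25.3% and 24.7%), it would be about 89%, a figure flattered by the fixed absolute margin. The primary outcome also ends at week 8 of a trial that runs to week 32, and the article does not say which period the 20% covers. The shortfall is therefore conditional. But adding patients for dropout only makes sense if dropouts are taken as lost to the primary analysis, and on that premise the allowance is too small.

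**The effect is negligible beside the uncertainty in the inputs.** Its small size is accepted. Moving the EA rate one point either way, to 30.6% or 32.6%, moves the evaluable number to about 280 or 196 per group. That argues for a low rank, not for leaving a wrong statement in place.

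**What a reader might wrongly infer.** One might conclude that the trial is materially underpowered or must enrol more patients. The figures do not support that: at the planned 280 per group the loss is about one point of power, and the target of 80% is kept up to 17–18% dropout.

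**Conclusion.** The sufficiency claim is wrong on its natural reading, and the error is minor. At the printed rates the design needs 233 evaluable and 292 randomised per group (230 and 288 with 31.67%). The stated 276 is 12 to 16 per group too few; the planned 280 is 8 to 12 too few. Power at 20% dropout is 1.3 to 1.7 points below target at 276, and 0.8 to 1.2 points below at 280.

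This rests on the article's own rates, margin and error levels, the normal approximation, equal groups, and dropouts contributing no primary-outcome data. It takes the 31.6% as given. The Background reports the pilot figure for spontaneous bowel movements after 8 weeks, not for complete ones averaged over weeks 3–8; that is a separate question and is not settled here.

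**What to change.** Replace the sample-size sentence with:

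> The inputs require 233 evaluable per group, i.e. 292 per group allowing for 20% dropout; the planned 280 per group gives about 79% power at 20% dropout, or 80% power at up to about 17% dropout, assuming dropouts contribute no primary-outcome data.

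If 31.67% is the intended EA rate, print that rate and use 230, 288 and about 18% instead. The two sets should not be mixed.

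The cost is one sentence and a stated power about one point less favourable. No added enrolment is needed. If the sponsor prefers to keep 80% power at 20% dropout, the price is 16 to 24 more patients in total.
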